#### Recruitment

Initial recruitment will begin in Brisbane in mid-2026, followed by rollout to other sites shortly thereafter. Recruitment will be conducted through antenatal clinics at the listed study sites, employing a range of methods including flyers/posters, newsletters, social media and websites of partner organisations. Where feasible, experienced Indigenous health team members, such as midwives, Indigenous research assistants and Aboriginal health workers, will identify and approach potential pregnant individuals and their partners (if applicable).

Recruitment at hospitals will involve the screening of medical records to assess potential participants’ eligibility based on the study criteria, particularly that the mother is carrying an Indigenous infant in her pregnancy. This process will also ensure care is taken not to contact individuals who may have recently experienced an unexpected or adverse pregnancy complication, eg, miscarriage, stillbirth, termination or fertility issues, as this could trigger discomfort or emotional distress. Potential participants will be contacted either face-to-face, via phone or email. Those who express interest in the SFS will receive a Participant Information Sheet and Consent Form (PICF), along with a link to access the SFS Participant Information Video. An Indigenous member of the study staff will then arrange to discuss the study in detail and address any questions, preferably in a face-to-face setting. Potential participants will be advised that participation in the study is entirely voluntary, and individuals can withdraw at any time. The consent process will also explain the nested family support programmes, and parents will have the option to self-refer at any time and allow data linkage with SFS. The written consent of the pregnant participant will include the consent of her infant/young child. Parental/guardian consent may be sought from some young participants (between 16 and 18 years) if deemed necessary by the research team, but only when the youth provides verbal consent to participate in the study. Consent will be obtained in a culturally sensitive manner, including the use of a Participant Information Video recorded by ISC members and the study team, prepared using accessible language to support potential participants who may appreciate support in understanding the complexity of the study.

Participating families will be offered a gesture of appreciation for their time, particularly where an in-person study visit is completed. Incentives may vary across study sites to reflect the unique needs of each community; however, items could include grocery vouchers, pre-paid parking vouchers (if paid parking is needed to access the service), a tote bag and toys. All incentives will be approved by the governing Human Research Ethics and Governance Safety Committee (HREC) prior to being offered to participants.

While full participation in the study is encouraged, some participants may choose to withdraw. Participants who formally withdraw from SFS may request the return or destruction of their biological samples at no personal cost, provided these have not yet been shared with collaborators or used in sub-studies. Following withdrawal from the study, participants will also have the option to either allow the continued use of their previously collected data or request its secure removal from the study dataset.

#### Study regimen

Data will be collected at multiple points throughout the study (figure 2, online supplemental table 1): < 28 weeks gestation, ≥ 28 weeks gestation, at the time of delivery, during the post-delivery period (in the hospital ward), at 6 weeks postpartum and at regular intervals throughout early childhood (from 3 to 36 months CA). Follow-up assessments will continue annually through early childhood.

**Figure 2 F2:**
[figure not shown]
The Strong Families Study recruitment and study visit timeline for participating families. (Note: A detailed description of data collected at each study visit is provided in the online supplemental
table
1).

Following consent, questionnaires will be delivered in person with the help of an Indigenous research assistant or health worker, where possible. A phone option will, however, be made available if requested. In the first two visits, the pregnant participant and, if applicable, their partner complete a series of questionnaires and biological sample collections and undergo initial physical measurements, such as blood pressure and weight. Following birth, the first set of neonatal data is collected, including body measurements and a chart review conducted by a midwife. Subsequent in-person visits will occur throughout the study period, except between 12 and 16 weeks postpartum during which parents are asked to record a 3-min video of their baby’s spontaneous movements for neurodevelopmental assessment (on the General Movements Assessment) (figure 2).^36 37^ Child neurodevelopmental assessments will continue to occur at each visit postbirth. Infants with a confirmed or high chance of a neurodevelopmental disability will be referred to the appropriate family support programmes available within the SFS.^27^,^29^

At the request of the ISC, all study surveys and instruments will be delivered in-person as the first preference using a yarning method, which encourages more informal and relaxed discussions between researchers and participants.^38^,^40^ Furthermore, a health education component will be embedded into the yarns following data collection to increase health literacy and promote healthy behaviours to grow health knowledge in participants of the study. To ensure all team members are appropriately trained and consistent in their approach, yarning guides co-designed by the ISC will be embedded within the electronic data collection forms used for the surveys.

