**Methods and analysis:**

The Strong Families Study is a co-designed prospective longitudinal birth cohort study that will follow 400 Indigenous families in Queensland from pregnancy until the child reaches 5 years of age. Eligible participants include pregnant individuals (<28 weeks’ gestation) whose children may identify as Aboriginal and/or Torres Strait Islander, along with their partners (if applicable). Data will be collected at multiple timepoints: during gestation, at delivery, postpartum, every 6 months until the child is 36 months (corrected age, CA) and annually until age 5 years. These will be collected by Aboriginal health workers using validated and culturally appropriate tools across different health themes. The study will incorporate health literacy throughout, as well as referrals to two nested family support programmes to support families and assist with the developmental outcomes of their children when and if required. Effects across health themes will be analysed with a focus on strengths, positive trajectories and holistic well-being of Indigenous families, moving beyond deficit-based narratives.

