### Study procedure

#### Study eligibility

Pregnant individuals who are less than 28 weeks of gestation and whose children may identify as Aboriginal and/or Torres Strait Islander, along with their partner (if applicable), will be eligible to participate in the study. To ensure the cohort is representative of the broader Queensland population, adoptive families, same-sex couples, single mothers or widowed mothers will also be invited to participate, including individuals with underlying health conditions. In many regions, English may not be the first language for Indigenous communities; however, due to the large number of Indigenous languages across Queensland, participation will be limited to individuals who can understand English. Exclusion criteria include participants under 16 years of age and those unable to provide informed consent.

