A parenting support programme will be offered that focuses on social and emotional well-being called PACT Online, grounded in Acceptance and Commitment Therapy. It has been tested with parents of children diagnosed with or with a high likelihood of neurodevelopmental disability or developmental delay and was designed to be flexible and appropriate to supporting all parents.^27^ This programme is directly offered to parents at 3 months CA, but families can self-refer at any point during the study (figure 2, online supplemental figure 1). Within this study, a First Nations PACT Online package will be codesigned. For infants aged <12 months CA in the study who have a high chance of adverse neurodevelopmental disability including cerebral palsy, autism or fetal alcohol spectrum disorder, a referral will be offered to families to participate in the Learning through Everyday Activities with Parents Study (LEAP) (figure 2, online supplemental figure 1). LEAP is a randomised early support trial delivered in the home by Indigenous family support workers. Compared with a health advice programme, it includes goal-directed skill training, responsive parenting, environmental enrichment through learning games and parent educational modules.^28 29^

At regular intervals, data linkage between the SFS database and the LEAP and PACT Online teams will take place to enable analysis of the family support programmes within the context of the SFS study. To ensure accurate referral processes, parents’ samples and questionnaires will be regularly reviewed for signs of clinically relevant findings or having an increased chance of developing a clinically relevant disease (see online supplemental figure 1 on flow chart for infant testing and referral processes in the SFS). Where family support programmes are required but outside the scope of the study, access to services, including liaising with the primary care team, will be facilitated by the study team.

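### The General Movements video is timed in weeks since birth while child follow-up from 3 to 36 months runs on corrected age, so infants born preterm would be recorded at a younger corrected age

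*Protocol article*

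**What the plan says.** The Study regimen section describes the visits after birth as in-person, "except between 12 and 16 weeks postpartum during which parents are asked to record a 3-min video of their baby". It gives the purpose of the recording as the baby's "spontaneous movements for neurodevelopmental assessment (on the General Movements Assessment").

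The rest of the early-childhood schedule uses a different scale:

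- Study regimen: data are collected "at 6 weeks postpartum" and then "at regular intervals throughout early childhood (from 3 to 36 months CA"). One sentence uses both terms, so they are distinct scales.
- Abstract, Methods and analysis: follow-up is "every 6 months until the child is 36 months (corrected age, CA) and annually until age 5 years".
- Data collection, on LEAP: "For infants aged <12 months CA in the study who have a high chance of adverse neurodevelopmental disability", families are offered referral.
- Data collection, on PACT Online: "This programme is directly offered to parents at 3 months CA".

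The Study eligibility section admits pregnancies below 28 weeks and sets no limit on gestational age at birth. It says: "Exclusion criteria include participants under 16 years of age and those unable to provide informed consent". Infants born preterm are therefore in the cohort.

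**The concern.** Weeks postpartum and corrected age agree only for births at or near term. The video falls just where the schedule changes from the postpartum scale to corrected age, yet it stays on the postpartum scale, and nothing in the text says that its weeks are corrected. A site following the sentence as written would record an infant born preterm at a younger corrected age than an infant born at term.

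The recording serves neurodevelopmental assessment. The same paragraph goes on to say that infants with a confirmed disability, or a high chance of one, are referred, and a high chance before 12 months corrected age opens the route to LEAP. If the age at observation moves with gestational age, classification and referral can move with it. Gestational age at birth belongs naturally among the neonatal and birth outcomes that the Introduction lists as an aim. It may also lie between the perinatal exposures and the child's development.

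**Working it through.** The plan has no figure of its own to reproduce here. The check is age arithmetic.

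**Inputs from the article**

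- Video window: 12 to 16 weeks postpartum (Study regimen).
- Start of the corrected-age series: 3 months (Study regimen).

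**Inputs assumed, because the article does not give them**

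- Term reference: 40 weeks.
- The example gestations below.
- One month = 365.25 / 12 / 7 = 4.348 weeks, so 3 months = 13.04 weeks.

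**Step 1. Put the window on the corrected scale.** Corrected weeks = weeks since birth − (40 − gestation at birth). For birth at 32 weeks the shift is 40 − 32 = 8, so the window is 12 − 8 = 4 to 16 − 8 = 8 corrected weeks.

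**Step 2. Do the reverse.** If 12–16 weeks were meant as corrected age, weeks since birth = corrected weeks + (40 − gestation). For birth at 32 weeks this is 20 to 24.

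| Gestation at birth (weeks) | Corrected age if the window is postpartum, as written (weeks) | Time since birth if the window were corrected (weeks) |
|---|---|---|
| 40 | 12–16 | 12–16 |
| 37 | 9–13 | 15–19 |
| 36 | 8–12 | 16–20 |
| 34 | 6–10 | 18–22 |
| 32 | 4–8 | 20–24 |
| 30 | 2–6 | 22–26 |
| 28 | 0–4 | 24–28 |

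**Step 3. Compare the two readings.** On the corrected scale, the window as written shares 4 weeks with a 12–16 week corrected window for birth at 40 weeks and 1 week for birth at 37. For birth at 36 weeks it only touches the edge, at 12 weeks. For earlier births the two do not meet.

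**Step 4. Compare with the 3-month point.** A window of 12–16 corrected weeks is 12 / 4.348 = 2.8 to 16 / 4.348 = 3.7 months, which contains 3 months corrected age. As written, the window for birth at 36 weeks closes at 12 corrected weeks, before 13.04. The shift grows by one week for each week of earlier birth, so it is small just below 37 weeks and large for very preterm birth.

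**What cannot be computed.** The article gives no expected share of preterm births, no age range over which the assessment is valid, and no list of the components of the primary outcome. A rate of misclassification cannot be derived without these.

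**The case against.** The strongest reply is that the operative schedule is not visible. The sentence on the video cites figure 2, and visit detail is referred to supplemental table 1. The list of timepoints in the Study regimen section has no separate contact at 12–16 weeks; it passes from 6 weeks postpartum to 3 months corrected age. Since 12–16 weeks is 2.8–3.7 months, the video may simply be the 3-month corrected-age timepoint, loosely worded. That is possible, and it limits the point to the text as it stands. It does not remove it: the visible sentence states the other scale and would still need correcting.

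It is also fair to say that corrected age is not universal elsewhere. The 6-week contact is on the postpartum scale, and the annual visits to age 5 carry no stated scale. The contrast holds for 3 to 36 months and for the LEAP limit.

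Four stronger readings are tempting, and the article does not support them:

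- A reader might infer that the main association is biased. The Sample size and statistical power section names a neurodevelopmental primary outcome but does not say that the video defines it, and child assessments continue at each visit after birth. Without a valid age range, neither direction nor size of error can be shown.
- A reader might infer that the video and the 3-month corrected-age contact cannot both be carried out as written. Nothing says that they must be one visit. The video is recorded by parents, and the PACT Online offer is a programme offer that does not depend on it.
- A reader might set an assumed number of preterm infants against the 20 expected primary events (5% of 400). The preterm share would be a guess, it would mix shifts of days with shifts of many weeks, and the comparison would not measure misclassification.
- A reader might ask for the primary association to be rerun without preterm infants. That restricts on a possible mediator, changes the quantity estimated and would not isolate an effect of video timing.

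**Conclusion.** The point holds as an inconsistency of age scale in the current text, with a definite effect on age at recording. Followed as written, the video is made at 8–12 corrected weeks for birth at 36 weeks, 4–8 at 32 and 0–4 at 28, against 12–16 at term. This rests on a 40-week term reference and on reading postpartum as time since birth, which is how the Study regimen section uses the word for the 6-week contact.

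The consequence is a possibility, not a demonstrated bias: neurodevelopmental classification and referral can come to depend on gestational age at birth, by an amount that the article does not allow anyone to calculate. If figure 2 and supplemental table 1 already give corrected age, what remains is a wording error. It is still worth correcting before recruitment starts in mid-2026, because age at recording cannot be changed afterwards.

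**What to change.** Reconcile the Abstract, both statements in the Study regimen section, the programme timings in the Data collection section, figure 2 and supplemental table 1, so that the video window is on one stated age scale consistent with the 3 to 36 month assessments. The study's clinical leads should settle which scale that is; this review takes no view on it.

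Record both chronological and corrected age at each child assessment, so that age at observation is available to any analysis of neurodevelopmental classification or referral.

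The cost is a wording change in the schedule and one derived variable.

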##### Data collection

The SFS focuses on the prioritised health themes determined through a collaborative co-design process by the ISC. They include social determinants of health; parenting; social and emotional well-being; early childhood development; chronic disease management (particularly focusing on diabetes, cardiovascular disease, bowel care, nutrition, physical exercise and respiratory disease); a strong cultural foundation for health which incorporates culturally safe pregnancy care and culturally responsive healthcare; and health education (figure 3, online supplemental material 1). All themes address health aspects relevant to both men’s and women’s health and will be delivered separately in a culturally appropriate manner.

**Figure 3 F3:**
[figure not shown]
Health themes chosen by the Indigenous Steering Committee and their corresponding questionnaires for participants in the Strong Families Study. (Note: A detailed description of each tool (with citations) is provided in the online supplemental
material
1).

Biological samples, of blood and urine, along with physical measurements, will be collected throughout the study period. Data collection will also include participant questionnaires and routinely gathered clinical information from medical records, such as medical history, medication usage and antenatal/perinatal data. The survey instruments used in the SFS have received approval from the ISC and will incorporate both validated and culturally appropriate tools, where available (figure 3, online supplemental material 1).

Health education within the SFS is framed not as a data collection theme, but as an act of reciprocity, providing meaningful knowledge and support back to the community across the various health themes. This will be embedded throughout the study as well as a referral to the two nested family support programmes. The ISC has requested that health education be delivered by the research team during each study visit, connected to the purpose of various research themes and data surveys. This will increase the health literacy of families in the study. Health education scripts have been developed for all research staff, and the ISC has reviewed and approved these.

A parenting support programme will be offered that focuses on social and emotional well-being called PACT Online, grounded in Acceptance and Commitment Therapy. It has been tested with parents of children diagnosed with or with a high likelihood of neurodevelopmental disability or developmental delay and was designed to be flexible and appropriate to supporting all parents.^27^ This programme is directly offered to parents at 3 months CA, but families can self-refer at any point during the study (figure 2, online supplemental figure 1). Within this study, a First Nations PACT Online package will be codesigned. For infants aged <12 months CA in the study who have a high chance of adverse neurodevelopmental disability including cerebral palsy, autism or fetal alcohol spectrum disorder, a referral will be offered to families to participate in the Learning through Everyday Activities with Parents Study (LEAP) (figure 2, online supplemental figure 1). LEAP is a randomised early support trial delivered in the home by Indigenous family support workers. Compared with a health advice programme, it includes goal-directed skill training, responsive parenting, environmental enrichment through learning games and parent educational modules.^28 29^

At regular intervals, data linkage between the SFS database and the LEAP and PACT Online teams will take place to enable analysis of the family support programmes within the context of the SFS study. To ensure accurate referral processes, parents’ samples and questionnaires will be regularly reviewed for signs of clinically relevant findings or having an increased chance of developing a clinically relevant disease (see online supplemental figure 1 on flow chart for infant testing and referral processes in the SFS). Where family support programmes are required but outside the scope of the study, access to services, including liaising with the primary care team, will be facilitated by the study team.

To support retention over the 5-year follow-up, we will prioritise in-person, culturally safe data collection using a yarning approach, supported by flexible scheduling, telehealth or phone options, and alignment with existing antenatal or paediatric appointments. Retention will be strengthened through sustained, trusting relationships fostered by ACCHOs and partnering hospitals; regular personalised contact (SMS, calls, emails and periodic check-ins); and routine updates to contact details, including alternative contacts. Reminder messages will be sent for upcoming visits, and site-approved appreciation or incentives will be offered where appropriate. We will also create a positive participant experience by ensuring visits are welcoming and culturally respectful and by acknowledging family and child milestones to support ongoing engagement.

##### Sample size and statistical power

The sample size of 400 families followed prospectively was chosen to provide sufficient power to examine associations between perinatal strengths/risk factors and pregnancy, birth and early childhood outcomes. Assuming approximately 5% of the cohort will have the primary outcome of ‘chance of cerebral palsy/autism spectrum disorder/neurodevelopmental outcome’, this sample gives 80% power (α=0.05) to detect absolute differences of ≥8 percentage points between binary risk factor groups. For more common binary outcomes, differences of >28% can be detected. For continuous outcomes, we will be able to identify between-category differences of >0.3 SD (Z-score units). These estimates are conservative, as repeated measurements over time and mixed-effects models will further improve precision.

